### Sample size

Primary outcomes are nausea, mucositis, constipation and fatigue as assessed by the RSCL items labelled ‘nausea’, ‘sore mouth/difficulty swallowing’, ‘constipation’ and ‘tiredness’ respectively. All items have a possible scale range of 1 to 4 (corresponding to a rating of ‘not at all’, ‘a little’, ‘quite a bit’ and ‘very much’ respectively) with higher scores indicating a higher levels of burden or impairment. These outcomes were chosen because they are common in patients receiving chemotherapy, are targeted by the PRISMS intervention and have demonstrated improvement following Telehealth interventions [33].

Sample size calculations were based on 80 % power, a 2-sided independent-samples *t* test with an alpha level of 0.05 and a standardised effect size of 0.4. In the absence of minimal important difference estimates for the RSCL, or any other symptom assessment tool validated for use in cancer patients, evidence-based effect sizes for the EORTC QLQ-C30 symptom scales and individual items were used as a guide [75, 76]. In this case, for all QLQ-C30 scales/items excepting the dyspnoea item, a standardised effect of 0.4 represents the lower threshold of a medium-sized clinically relevant difference between groups of cancer patients. Given these specifications, a total of 200 patients (100 per arm) is required. Assuming attrition of up to 10 %, a total of 222 patients (111 per arm) are needed at baseline.

### Recruitment

Based upon recruitment/retention statistics collected in the Phase II trial at the Melbourne site in 2012–13, and upon the predicted eligible patient population presenting at the Brisbane site, we estimate that around 108 patients will be recruited in 12 months across the 2 sites with total recruitment time of approximately 25 months.

### Analyses

#### Quantitative

All data will be entered into Microsoft Excel 2003 (or higher) (Microsoft Inc., Redmond, WA, USA) then imported into SPSS Windows Version 21 (or higher) (SPSS, Chicago, IL, USA) for scoring and analysis. R version 3.0.1 (or higher) and the R package ‘ggplot2’ will be used to prepare all graphs and plots [77].

Prior to formal analysis, descriptive statistics and graphical displays will be used to identify missing and out-of-range values, assess the plausibility of means and standard deviations (SDs) for all variables and identify outliers and screen continuous variables for normality.

#### Recruitment bias

Recruitment bias will be assessed by comparing demographic and clinical variables of patients who consent to participate and those who decline participation using *t* tests (or Mann-Whitney *U*) and chi-squared (or Fisher’s exact) tests as appropriate.

#### Differential attrition

Possible differential attrition will be assessed by comparing baseline characteristics of drop-outs and continuing participants using *t* tests (or Mann-Whitney *U* tests) and chi-squared (or Fisher’s exact) tests as appropriate.

#### Outcome analyses

Analyses will be by intention-to-treat. Primary and secondary outcome analyses will be carried out by fitting a linear mixed model to each outcome separately using all available data. A cell mean model (suppressing the default intercept) will be used to estimate mean scores for each group (study arm) by time combination; all models will include a fixed group by time effect and no random effects [78]. An unstructured covariance type will be used to model the covariance structure among repeated measures and all models will be estimated by maximum likelihood. The primary analysis will be group comparisons at post-baseline time points; these will be performed using contrasts within the proposed models. The group by time interaction will be used to assess the overall pattern of change [79]. A ‘toxicity’ by group by time interaction will be added to each model to assess whether participants receiving chemotherapy protocols classified as either ‘low-toxicity’ or ‘high toxicity’ respond differently to the PRISMS intervention. Adjusted analysis including using baseline responses to study measures and the remaining stratification factors will also be investigated.

After inspection of the data, the appropriateness of suggested methods will be assessed and revised as necessary. Specific emphasis will be placed on assessing models proposed for the analysis of primary and secondary outcomes that are measured on an ordinal scale; that is, nausea, mucositis, constipation and fatigue as assessed by the RSCL. When applied to ordinal outcomes, models for continuous outcomes can yield biased estimates of regression coefficients. When the distribution of scores on ordinal variables is highly skewed, this bias may be large and the use of methods specifically designed for ordered data is recommended [80]. In this case, if graphical exploration of the data and/or regression diagnostics indicates violation of model assumptions, relevant analyses will be carried out by fitting an ordinal logistic generalised linear mixed model to each outcome separately using methods described by Hedeker [81]. In brief, fully parameterised models will include fixed effects for group, time plus a group by time interaction, as well as random subject and time effects.

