### Registration and randomisation

Following consent and completion of the Baseline Questionnaire, the DM at the coordinating site will register the participant, confirming all eligibility/registration details and will allocate a participant identification number. The participant will be randomised by the DM using a centralised randomisation database 1:1 to either the control or intervention groups. Participants will be stratified according to treating hospital, cancer type, treatment toxicity (high versus low as predetermined by clinical investigators based on the likelihood of patients developing febrile neutropenia during treatment) and receipt of previous chemotherapy treatment (received no previous chemotherapy versus received some form of previous chemotherapy either orally or intravenously). Minimisation will be used to balance randomisation across strata (also known as baseline adaptive allocation) – this is a dynamic allocation process where the probability of a patient being allocated to a particular arm varies for each patient being randomised, depending on the patients who have previously been randomised in the study and their status at the stratification factors [45, 46]. No sequence is generated in advance, instead the randomisation database generates a set of probabilities the particular patient will be allocated to an arm, based on the above set of pre-specified rules. The minimisation process aims to allocate equal numbers of patients to each arm simultaneously over many strata. The multiple strata are combined into a score for the degree of imbalance between arms, and then the allocation is made based on a coin algorithm.

Participants randomised to the intervention arm will be scheduled for their first session with an intervention nurse for education and training in the use of the Android tablet.

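### The primary mid-cycle 2 contrast omits the baseline score and the minimisation factors, so it is mildly conservative and less precise than it could be, although the planned 80% power is still met

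*Protocol article*

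**What the plan says.** All references are to the protocol article.

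- **Allocation (Registration and randomisation).** "Minimisation will be used to balance randomisation across strata". The factors are given as follows: "Participants will be stratified according to treating hospital, cancer type, treatment toxicity", with previous chemotherapy as the fourth.
- **Model (Outcome analyses).** Each outcome gets its own linear mixed model, set up as cell means for every arm and time: "all models will include a fixed group by time effect and no random effects". The covariance is unstructured and estimation is by maximum likelihood. The primary analysis is the set of arm contrasts at post-baseline times; the Primary hypothesis section fixes mid-cycle 2 as the time point.
- **Toxicity (same section).** It is added to each model in a three-way interaction with arm and time, to see whether response differs between toxicity classes.
- **Everything else (same section).** "Adjusted analysis including using baseline responses to study measures and the remaining stratification factors will also be investigated".
- **Fallback (same section).** If model assumptions fail, an ordinal logistic mixed model is fitted, with fixed effects for group, time and their interaction.
- **Sample size.** The assumed effect is 0.4 SD, and the test is unadjusted: "Sample size calculations were based on 80 % power, a 2-sided independent-samples *t* test with an alpha level of 0.05 and a standardised effect size".

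**The concern.** Minimisation forces the arms to resemble each other on four factors. If those factors predict symptom burden, the balance removes part of the chance variation in the difference between arms. A model without the factors still counts that variation as noise. Its standard error then exceeds the true sampling error and the test rejects too rarely under the null.

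The baseline score raises a separate issue. It is collected before randomisation, yet a cell-mean model with separate baseline means in each arm does not use it to sharpen the mid-cycle 2 contrast. The resulting standard error is correct for that contrast but larger than it need be.

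What is at stake is precision that the trial could have without recruiting anyone further, and a test that runs at its nominal level.

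**Working it through.** **Inputs.** From the Sample size section: two-sided alpha 0.05, 80% power, effect 0.4 SD, 100 per arm evaluable, 10% attrition, 222 enrolled. From Registration and randomisation: 1:1 allocation by minimisation on four factors. Assumed, because the article gives no values: the correlation r between baseline and mid-cycle 2 item scores (0.1 to 0.5), and the share R² of outcome variance explained by the minimisation factors (5% to 20%).

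**1. The plan's own figure.** n per arm = 2(1.96 + 0.8416)²/0.4² = 98.1, so 99. The t-based solution is 99.08, so 100. This agrees with "a total of 200 patients (100 per arm) is required". Then 200/0.9 = 222.2, against the stated 222. Power at 100 per arm is 80.7% (normal approximation) or 80.4% (t). The figure reproduces and assumes no covariate adjustment.

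**2. Does the unstructured covariance already use the baseline?** The cell-mean model was fitted to simulated data with baseline among the repeated measures (correlation 0.5 between all times, 300 runs).
- Complete data, 100 per arm: the mid-cycle 2 contrast equalled the raw difference in means (largest discrepancy 2 × 10⁻¹⁶). Its empirical SE was 0.146, against 0.121 with baseline as a covariate.
- 222 enrolled, 10% dropping out after baseline: 0.135 for the cell-mean contrast, against 0.122 with the covariate. The model recovers some information for those who drop out, but not the covariate gain.

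**3. Minimisation factors omitted.** Under full balance the true SE is √(1 − R²) times the model SE, so the size of the nominal 5% test is 2[1 − Φ(1.96/√(1 − R²))].

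| R² (assumed) | 1.96/√(1 − R²) | Size |
|---|---|---|
| 5% | 2.011 | 4.4% |
| 10% | 2.066 | 3.9% |
| 15% | 2.126 | 3.4% |

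Simulated minimisation (assumed 0.8 biased coin, N = 200, 2,500 runs per setting, r = 0.3) gave a model SE of 0.141. The true SEs were about 0.137, 0.135 and 0.130 at R² of 5%, 10% and 20%. Size was 4.4%, 4.4% and 3.1% unadjusted, and 5.0%, 5.6% and 5.2% with the factors in the model. Monte Carlo error at a true 5% is √(0.05 × 0.95/2500) = 0.4 points.

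**4. Baseline score omitted.** Adjustment multiplies the SE by √(1 − r²). Power = Φ(0.4/[√(2/100) × √(1 − r²)] − 1.96).

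| r (assumed) | SE ratio | Power at 100 per arm | n per arm for 80% |
|---|---|---|---|
| 0 | 1.000 | 80.7% | 99 |
| 0.1 | 0.995 | 81.1% | 98 |
| 0.2 | 0.980 | 82.3% | 95 |
| 0.3 | 0.954 | 84.3% | 90 |
| 0.4 | 0.917 | 87.0% | 83 |
| 0.5 | 0.866 | 90.4% | 74 |

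The exact t calculation gives 83.9%, 86.7% and 90.1% at r = 0.3, 0.4 and 0.5.

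**5. Cost in parameters.** Hospital 1, diagnosis 2 (three types in the inclusion criteria), toxicity 1 and previous chemotherapy 1 make 5. Baseline by time over mid-cycles 2, 3 and 4 adds 3. The total is 8.

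**The case against.** The strongest reply is that nothing planned is lost. The trial was sized on an unadjusted t test, the primary contrast is unadjusted, and the two match. This stands: the loss is of attainable power, not of the 80% promised.

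It can also be said that both effects may be small. A pre-chemotherapy rating on a single four-point item may correlate weakly with the same item at mid-cycle 2, and at r = 0.1 to 0.2 the gain is under 2 points of power. A simulated size of 4.4% lies within about 1.5 Monte Carlo standard errors of 5%. These limits on magnitude stand. The direction does not depend on them, and the closed form gives the same sign whenever the factors are prognostic.

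The detail of an adjusted analysis may properly be left to an analysis plan that is not shown. That is fair for its exact form. Its rank as an addition to the unadjusted contrast, however, is fixed in the article.

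Four stronger readings are tempting, and the article does not support them.

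- A reader might infer that the trial is underpowered or that false positives are inflated. The planned power is met, and the size error is conservative.
- A reader might infer that the standard error is wrong on both counts. That is strictly so only for the minimisation factors; without the baseline score it is valid.
- A reader might infer that two rival primary results will exist. The Outcome analyses section names the post-baseline contrasts as primary and the adjusted analysis as additional.
- A reader might infer that toxicity is ignored. It has its own interaction model, which is why the text speaks of the remaining factors, but that model tests effect modification and does not adjust the primary contrast.

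**Conclusion.** The point holds as a worthwhile improvement in efficiency and calibration, not as a flaw that invalidates the primary analysis. Omitting the minimisation factors makes the test mildly conservative, with a size of about 4.4% to 3.4% if they explain 5% to 15% of outcome variance under full balance. Omitting the baseline score forgoes under 2 points of power at r = 0.1 to 0.2 and about 10 points at r = 0.5.

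Confidence is high in the direction and limited in the magnitude, because the article gives neither r nor R². All these figures belong to the linear model and do not carry over to the ordinal fallback.

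**What to change.** Make the adjusted mid-cycle 2 contrast primary. Model the post-baseline item scores with arm by time, baseline item score by time, and fixed effects for hospital, diagnosis, toxicity class and previous chemotherapy, and keep the unstructured covariance. Report the unadjusted cell-mean model as a sensitivity analysis, and keep the toxicity interaction model for its stated purpose.

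If the ordinal logistic mixed model is used instead, carry the same covariates into it. State that its conditional odds ratio is a different estimand from the mean difference.

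The cost is a change of wording and about 8 extra parameters over the three mid-cycle times, small against 200 evaluable patients. The minimisation factors are known at randomisation and the baseline responses are already planned data, so nothing further need be collected and the sample size need not change.

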#### Exploratory analyses

Linear regression models will be used to explore predictors of health-related quality of life and psychological distress at baseline. Growth curve models will be used to explore associations between baseline characteristics and longitudinal outcome data in the control group. Linear regression models will also be used to explore predictors of health services utilisation.

#### Intervention compliance

Frequency statistics (i.e. raw counts and averages) will be used to summarise data relevant to patient/nurse intervention compliance. This data will come from two sources: the electronic log of the PRISMS system and digital recordings of face-to-face and phone intervention sessions.

#### PRISMS electronic log files

With respect to *patient data* this will include: frequency of < 2 symptom questionnaires being completed within a 24-hour period; Frequency of ‘missing alerts’ generated (i.e. no symptom questionnaires submitted within a 24-hour period); Frequency of missing weekly self-care use questionnaires.

With respect to *nursing data* this will include: frequency of red alerts responded to within designated timeframe (i.e. 15 minutes) as measured by login to secure server; frequency of amber alerts responded to within designated timeframe (i.e. 8 hours) as measured by login to secure server; frequency of missing alerts responded to within designated timeframe (i.e. 8 hours) as measured by login to secure server; frequency of documentation of actions taken in response to alerts and completion of checklists for scheduled interventions.

#### Digital recordings

A content checklist has been developed to assess ‘intervention completeness’ for each intervention time point. Checklists will be based on the nursing intervention manual as previously developed by the research team. A sub-set of recordings (20 %) will be listened to by 2 members of the research team and a percentage completeness figure calculated.

#### Economic evaluation

Cost utility analysis (a form of cost-effectiveness analysis), measures benefits in quality- adjusted life years (QALYS). This will allow for the comparison of efficiency of patients receiving the PRISMS intervention and those receiving Usual Care in terms of cost-per-QALY gained. Analyses will be undertaken both from a broad societal perspective in addition to a health care perspective.

The incremental cost of the intervention will be compared to the incremental health outcome improvement attributed to the intervention. Results will be expressed as cost per QALY gained (i.e. the incremental cost-effectiveness ratio (ICER) will be determined for patients receiving either the PRISMS intervention or Usual Care) within the trial period and projected beyond the trial period using appropriate economic modelling. Uncertainty in the cost and outcome data will be further evaluated via sensitivity analyses whereby key evaluation parameters (such as unit costs) are varied to assess the impact on study conclusions.

Economic measures for both benefits and costs utilised in these analyses include the EQ-5D as a utility measure of patient quality of life; the Health Services and Costs Questionnaire to determine use of health care services and medicines and; a medical record (MR) audit of both treating hospital records and any external hospital records (eg emergency admissions). More specifically, MR audits and the Health Services Usage and Costs Questionnaire will document: emergency room presentations, planned/unplanned hospital admissions, total bed days of care and reasons of hospitalisation, use of nursing/allied health resources, clinical investigations, medications prescribed (including chemotherapy and dose reductions and treatment delays), use of community health resources (eg general practitioners (GPs), allied health), use of alternative therapies, community services (eg meals on wheels); use of transport; days out of role (paid/unpaid) for both patients and carers, alongside any other costs incurred to patients/carers as a result of their cancer treatment. Data collection will cover both that paid for by the individual (before/without rebate) and also that paid for by third parties (eg rebated dollar amount by Medicare or private health insurance companies). Calculation of the cost of the PRISMS intervention itself will include only the costs of the intervention delivery (i.e. excluding development or research costs). Research team records (eg PRISMS website; data transmission costs, training time/materials) will be used to determine the cost of the intervention. Measured resource use will be valued using existing unit costs such as the National Hospital Cost Data Collection-Cost Report; Australian Refined Diagnosis Related Groups for inpatient health costs, Medicare Benefits Schedule for outpatient costs, Pharmaceutical Benefit Scheme for pharmaceutical costs and Australian Bureau of Statistics for estimates of Australian earnings for productivity effects.

### Ethical issues

The study protocol has been ethically approved by institutional ethical review committees at both participating sites (Peter MacCallum Cancer Centre Human Research Ethics Committee and Bellberry Human Research Ethics Committee for ICON Cancer Care). The rights and welfare of the participants will be protected according to the National Health and Medical Research Council of Australia’s National Statement on Ethical Conduct in Human Research. Clinical care and emergency medical services are provided by participating institutions. Data that is collected as part of the study will not be linked to any individual.

## Discussion

The proposed system combines cutting edge technology with systematic evidence-based, nursing consultation. It is internationally innovative and tailored to the real-time monitoring of CTx toxicities and the provision of tailored self-care to address individual needs. Given the aging of the Australian population and the consequent expected increase in people diagnosed with cancer, it is imperative to find cost-effective strategies to improve the quality and safety of cancer care in the community whilst improving patient outcomes. These systems are most critical where CTx treatment has a high-risk of toxicity and potentially life-threatening consequences leading to unplanned hospitalisations, such as with haematological malignancies, including leukaemia and lymphoma. The development of Telehealth systems and interventions which allow for the real-time remote monitoring and management of high risk patients during treatment are, therefore, a priority.

### Methodological rigour

This study will be the first technology-mediated nurse-led intervention study for cancer patients that meets the Consolidated Standards of Reporting Trials (CONSORT) criteria for randomised controlled trials [82] and fits within the MRC framework for the analysis of complex interventions [44]. Participants will be randomly allocated by a computer after eligibility assessment and the collection of baseline data. Intervention procedures will be strictly monitored for protocol adherence. The relatively short follow-up period will minimise dropout. Reasons for attrition will be recorded, and recruitment and dropout bias assessed. Blinding of patients and providers cannot be achieved with this study design. However, outcome assessment will be by patient self-report questionnaire, obviating the need for researcher blinding. A previous shortcoming of similar research [33] is the lack of knowledge of patient adherence to completing self-care behaviours when interpreting study outcomes. This system is, therefore, also unique in its ability to regularly measure patient adherence to self-care behaviours for key side-effects. Quantitative assessment of both nursing and patient intervention compliance will also be invaluable in guiding system or intervention changes needed to maximise system useability and intervention compliance for future studies.

As the intervention has been grounded in the current nursing models of patient care, alongside the development of detailed study training materials, the roll-out of the intervention to routine clinical practice following a successful Phase III trial could also be completed relatively efficaciously. The suitability of the system for both in-patient and out-patient treatment populations also makes it widely applicable to a range of chemotherapy treatment protocols.

The PRISMS intervention is innovative and tailored to the real-time monitoring of chemotherapy toxicities and the provision of tailored self-care to address individual needs. It is the first system designed to specifically monitor adult patients with haematological cancers undergoing chemotherapy. It is also the first randomised controlled trial of any Telehealth- mediated nurse-led intervention for cancer patients and builds from earlier ASyMS work and will, in tandem with the current large European (>1000 patients) ASyMS randomised controlled trial, add to our growing knowledge of the impact of these interventions on patient health outcomes and health system costs. Nursing interventions, combined with remote monitoring systems, such as those described in this protocol, are, therefore, likely to enable both more accurate symptom monitoring and management, combined with greater efficiency and effectiveness of nursing roles in haematology.

